## Abstract

**Background:**

In-hospital cardiac arrest has a poor prognosis despite active electrocardiography monitoring. The initial rhythm of approximately 25% of in-hospital cardiopulmonary resuscitation (CPR) events is pulseless ventricular tachycardia/ventricular fibrillation (VT/VF). Early defibrillation is an independent predictor of survival in CPR events caused by VT/VF. The automated external cardioverter defibrillator (AECD) is a device attached by pads to the chest wall that monitors, detects, and within seconds, automatically delivers electric countershock to an appropriate tachyarrhythmia.

**Study Objectives:**

• To evaluate safety of AECD monitoring in hospitalized patients.

• To evaluate whether AECDs provide earlier defibrillation than hospital code teams.

**Methods:**

The study is a prospective trial randomizing patients admitted to the telemetry ward to standard CPR (code team) or standard CPR plus AECD monitoring (PowerHeart CRM). The AECD is programmed to deliver one 150 J biphasic shock to patients in sustained VT/VF. Data is collected using the Utstein criteria for cardiac arrest. The primary endpoint is time-to-defibrillation; secondary outcomes include neurological status and survival to discharge, with 3-year follow-up.

**Conclusion:**

AECD monitoring is safe and likely results in earlier defibrillation than standard telemetry monitoring.

**Trial Registration:**

National Institutes of Health registration ID: NCT00382928

## Background

In-hospital cardiac arrest has a poor prognosis despite active electrocardiography monitoring. Part of the poor prognosis may be explained by slow response to a lethal arrhythmia.[1] The National Registry of Cardiopulmonary Resuscitation (NRCPR) has reported delayed defibrillation, which was defined as greater than 2 minutes, in more than 30% of cases of in-hospital cardiac arrest. This delay in defibrillation resulted in significantly lower probability of surviving to hospital discharge.[1]

The initial rhythm in about 25% of in-hospital cardiac arrest is ventricular tachycardia or fibrillation (VT/VF).[2] Early provision of good quality CPR and rapid defibrillation have the highest impact on survival for the victims of VT/VF cardiac arrest.[3] Early defibrillation is an independent predictor of survival in CPR events caused by VT/VF.[4,5] Delay in provision of defibrillation for 10 minutes renders CPR ineffective.[4] Each minute of delay in defibrillation increases the likelihood of death by 7% to 10% in cardiac arrest.[5] If defibrillation is provided within 3 minutes in in-hospital cardiac arrest, 38% survival to discharge is reported versus 21%, if defibrillation is provided after 3 minutes.[2] Addressing this delay, a program encouraging early defibrillation using automated external defibrillators (AED) in the hospital resulted in a 14-fold increase in survival for VT/VF cardiac arrest.[6]

Automated External Cardioverter Defibrillator (AECD; The PowerHeart CRM, Cardiac Science Inc., Seattle, WA) is a device attached to the chest wall by pads, monitors the electrocardiogram, and is capable of automatically delivering electric countershock to appropriate rhythms without operator intervention. Automated external cardioverter defibrillators have been studied in a few nonrandomized clinical trials. [7-9] They performed with a sensitivity of 100% and a specificity of 98.8% in a study conducted in the United States (n = 79) and a sensitivity of 100% and a specificity of 97.6% in an European study (n = 117).[7,8] We designed the current randomized trial to test the safety of AECDs in hospitalized patients and the performance compared to standard telemetry response.

## Methods

This study is a single center, randomized, prospective, trial in which, all patients admitted to the emergency department and telemetry unit of the Atlanta Veterans Affairs Medical Center (AVAMC), Decatur, Georgia are screened. Patient recruitment started in October 2006. Inclusion and exclusion criteria are presented in Table 1. Patients consenting to participate in the study are randomized to either standard electrocardiographic telemetry or standard telemetry augmented by AECD monitoring (Figure 1). Patients randomized to AECD monitoring have the AECD attached for the duration of their hospitalization while undergoing simultaneous telemetry monitoring. A log book is used to record the time of AECD attachment and to record whenever the AECD is detached from the patient. The AECD is programmed to deliver a single 150 Joule shock to VT/VF rhythms presenting above the rate of 170 beats per minute, after a 30 second delay. Study enrollment terminates when telemetry is discontinued. The primary endpoint is time-to-defibrillation in VT/VF cardiac arrest. The AECDs have the ability to measure the precise time of initiation of cardiac arrhythmias and of delivery of defibrillation. The secondary outcomes are survival to discharge and cerebral outcomes as measured by cerebral performance category scale (Table 2). Patients who survive cardiac arrest while participating in the trial will be followed for a period of three years for survival, internal cardioverter defibrillator (ICD) placement and cerebral performance. The Emory University Institutional Review Board (IRB) and the AVAMC Research and Development Committee approved the study.

**Table 1 T1:** Inclusion and Exclusion Criteria

**Inclusion Criteria**:
1. All patients admitted to telemetry ward and ER.
2. Age > 18 years.

**Exclusion Criteria**:

1. Pregnant women.
2. Patients with R wave less than 0.5 mV in lead II.
3. Patients with functioning ICDs.
4. Patients with cardiac pacemakers if oversensing by AECD is demonstrated (double counting of pacer spikes).
5. Patients with visible chest lesions that would prevent AECD pad placement.
6. Patients who are designated DNR.
7. Right bundle branch block.
8. Patients with Parkinson's disease.
9. Patients with seizure disorders.

**Additional Exclusion Criteria for Emergency Room**:

10. Patients with dementia and/or delirium.
11. Patients presenting with psychiatric complaints.
12. Patients who are agitated.
13. Patients presenting with trauma.
14. Patients unable to participate in the informed consent process.
15. Patients with respiratory rate greater than twenty.
16. Patients who report pain greater than four out of ten in the visual analog scale.

ER = emergency room; ICD = internal cardioverter defibrillator; AECD = automated external cardioverter defibrillator; DNR = do not resuscitate

**Table 2 T2:** Cerebral Performance Categories/CPC scale

**CPC 1**: Good cerebral performance – conscious, alert, able to work, might have mild neurologic or psychological deficit.

**CPC 2**: Moderate cerebral disability – conscious, sufficient cerebral function for independent activities of daily life. Able to work in sheltered environment.

**CPC 3**: Severe cerebral disability – conscious, dependent on others for daily support because of impaired brain function. Ranges from ambulatory state to severe dementia or paralysis.

**CPC 4**: Coma or vegetative state – any degree of coma without the presence of all brain death criteria. Unawareness, even if appears awake (vegetative state) without interaction with environment; may have spontaneous eye opening and sleep/awake cycles. Cerebral unresponsiveness.

**CPC 5**: Brain death – apnea, areflexia, EEG silence, etc.

EEG = electroencephalogram

**Figure 1 F1:**
[figure not shown]
Design of the AECD Trial. ED = emergency department; AECD = automated external cardioverter defibrillator; VT/VF = ventricular tachycardia/ventricular fibrillation.

### Data collection

Demographic and arrest data is collected according to Utstein guidelines and stored in a database designed with Microsoft access software (Microsoft Inc., Redmond, WA).

### Sample size

A total sample size of 40 patients per group will be recruited. There are approximately 40 true cardiac arrests per year on the telemetry ward. The expected time to defibrillation in the AECD group is to be 30 ± 30 seconds, whereas time to defibrillation in the standard of care group is 180 ± 180 seconds. The expected time to defibrillation in the AECD group will be programmed into the device. Time to defibrillation will be coded continuously in both groups. Using a two-tailed t-test to compare time to defibrillation between the groups, a sample size of 12 patients per group affords 81% power at alpha = 0.05. A total sample size of 40 patients per group will yield over 99% power for a two-tailed test at alpha = 0.05.

### Statistical analysis

The primary outcome will be time-to-defibrillation. Demographic and clinical categorical and continuous variables are compared for patients in the standard of care versus the AECD group at cardiac arrest. Baseline data will be expressed as mean ± SD for continuous variables, and frequencies for categorical variables. Differences in baseline characteristics between the groups will be examined by the use of χ^2 ^tests and two-sample t-tests, or, if assumptions are not met, by Fisher's Exact and Mann-Whitney tests for categorical and continuous variables, respectively. Time to defibrillation will be measured continuously in both the standard of care and the AECD group, then compared using a two-tailed t-test. Assumptions will be checked and analyses will be adjusted accordingly.

In addition a multiple logistic model will be used to analyze the secondary endpoints (survival of cardiac arrest, survival to discharge), considering all the available variables. The total sample size will limit this analysis; however, an exploratory forward stepwise selection procedure will be used with a p-value of at least 0.10 for entry and 0.05 for removal. All pairwise interactions between AECD use and the other variables in the final stepwise model will be tested. A Hosmer-Lemeshow test will be used to test goodness of fit. Odds ratios will be presented with 95% confidence intervals. Pearson residuals, deviance residuals, and influence statistics will be examined to assess model fit. Statistical analyses will be performed using SAS version 9.1.3.

Cerebral performance state (Table 2) will be measured using the cerebral performance categorization (CPC) scale and analyzed initially using χ^2 ^tests. If cell counts warrant, the 2 × 3 contingency table will be analyzed using exact methods and the mean score statistics (Q) will be used to compare cerebral performance status between the groups.

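### The only stated survival analysis is a stepwise search that neither guarantees the randomised arm a place in the model nor excludes post-randomisation variables, and its removal limit is stricter than its entry limit

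*Protocol article*

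**What the plan says.** The Statistical analysis section of the protocol article gives one method for survival of cardiac arrest and survival to discharge, a multiple logistic model built "considering all the available variables". The variables are chosen by a search: "an exploratory forward stepwise selection procedure will be used with a p-value of at least 0.10 for entry and 0.05 for removal". After the search, "All pairwise interactions between AECD use and the other variables in the final stepwise model will be tested". Odds ratios with 95% confidence intervals are to be reported. The section concedes that "The total sample size will limit this analysis".

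The other tests in that section cover baseline characteristics, time to defibrillation and cerebral performance category. None compares survival between the arms. The Data collection section says "Demographic and arrest data is collected according to Utstein guidelines", so the database holds variables that arise at the arrest, after randomisation. Time to defibrillation, the primary outcome, is recorded in both groups.

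**The concern.** Three features of the stated rule matter, in increasing order of importance.

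1. **The limits are the wrong way round.** A variable with p between 0.05 and 0.10 is good enough to enter and too weak to stay. The search can return to a model it has already visited, or stop early.
2. **The candidate set is unrestricted.** Nothing confines it to pre-arrest variables. Time to defibrillation lies on the path from device to survival, and the article's Background presents faster shock as the reason survival should improve. Adjusting for it removes the effect being sought.
3. **The randomised arm is not secured.** The interaction step takes for granted that AECD is in the final model, but the selection rule does not ensure this.

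At stake is the survival comparison itself. The Discussion faults earlier AECD studies for not evaluating survival, and says that continuing the trial will allow outcomes to be compared between the strategies.

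**Working it through.** **The plan's own figures.** The article states no power for the survival model. Its stated power is for the primary t-test, and that reproduces from 30 ± 30 s against 180 ± 180 s (difference 150 s):

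- 12 per group: SE = √((30² + 180²)/12) = 52.7; 150/52.7 = 2.85; power = Φ(2.85 − 1.96) = 81% (stated 81%).
- 40 per group: SE = 28.9; 150/28.9 = 5.20; power = Φ(5.20 − 1.96) = 99.9% (stated over 99%).

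These figures say nothing about survival.

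**Inputs for survival (assumptions).** The Background reports 38% survival to discharge when the shock comes within 3 minutes and 21% when it comes later. These are used as a proxy for the two arms. The number is 40 arrests per arm, whereas the Sample size section says only "A total sample size of 40 patients per group will be recruited".

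**Power for the arm.** Pooled rate = (0.38 + 0.21)/2 = 0.295.

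- SE under no effect: √(2 × 0.295 × 0.705/40) = 0.1020.
- SE under the effect: √((0.38 × 0.62 + 0.21 × 0.79)/40) = 0.1002.
- At 0.05: Φ((0.17 − 1.960 × 0.1020)/0.1002) = Φ(−0.298) = 38%.
- At 0.10: Φ((0.17 − 1.645 × 0.1020)/0.1002) = Φ(0.023) = 51%.

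An arm that must reach p ≤ 0.05 to stay would therefore be absent in about 1 − 0.38 = 62% of analyses. With fewer arrests, power at 0.05 falls to 21% (20 per arm) or 14% (12 per arm). Using the 39.3% and 22.2% quoted in the Discussion instead, with 40 per arm, gives 38% again.

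**Why a retained estimate is exaggerated.** The assumed odds ratio is (0.38/0.62)/(0.21/0.79) = 2.31. Expected counts are 15.2 survivors and 24.8 deaths against 8.4 and 31.6. The SE of the log odds ratio is √(1/15.2 + 1/24.8 + 1/8.4 + 1/31.6) = 0.507. To stay at 0.05, the observed odds ratio must exceed about exp(1.96 × 0.507) = 2.70, which is already above the assumed 2.31.

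**The gap between the limits.** At these same expected counts, the score statistic is 0.17/0.1020 = 1.667 (p = 0.095) and the Wald statistic is ln(2.31)/0.507 = 1.648 (p = 0.099). A trial that observed exactly the assumed effect would enter the arm and then remove it.

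**Simulation of the search.** 1,000 trials per setting, 40 per arm, 38% against 21%, ten null covariates (an assumption), score test to enter, Wald test to remove:

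| Entry / removal | Arm kept | Search revisits a model | Median arm OR when kept |
|---|---|---|---|
| 0.10 / 0.05 (as stated) | 39.6% | 52.5% | 3.9 |
| 0.05 / 0.05 | 38.2% | 6.2% | 3.9 |
| 0.05 / 0.10 | 37.4% | 0% | 4.2 |
| 0.10 / 0.10 | 53.2% | 7.7% | 3.8 |
| 0.10 / 0.15 | 49.1% | 0% | 3.8 |

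Revisiting disappears when removal is looser than entry. Retention at 0.10/0.05 is close to that at 0.05/0.05, so the 0.10 entry limit does almost no work.

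**Time to defibrillation as a candidate.** 600 trials per setting, with exponential times of mean 30 s and 180 s and survival depending on time alone. The log-odds of survival fall by 0.3, 0.5 or 0.8 per minute (assumed). Under the stated limits, time entered the final model in 53% to 86% of trials and the arm in 10% to 13%. The median arm odds ratio was 1.9 to 3.0 with arm alone, and 0.94 to 0.99 with arm and time both fitted.

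**The case against.** The case on the other side has force on several points.

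- **The limits.** A reader might infer that the reversed limits are what loses the AECD effect. The table does not support that: retention is about the same at 0.05/0.10. Nor should the phrase about a p-value of at least 0.10 be pressed as admitting only weak predictors; it is loose wording for a threshold.
- **Retention.** A reader might take the roughly 40% as the damage done by stepwise selection. It mostly reflects low power: an arm kept in by rule would be non-significant about as often. What selection adds is that the estimate and interval then go unreported, and that those reported are inflated.
- **The arm.** The interaction sentence speaks of AECD use and the *other* variables in the final model, which presupposes that AECD is there. The authors may well have intended to keep it. The text still gives no rule that does so.
- **Mediators.** The article never names time to defibrillation as a candidate. Its eligibility is inferred from unrestricted wording read with the Data collection section. A condensed article may leave the candidate list to a fuller document, but the wording it does give points to all variables.
- **AECD use.** One might infer an as-treated analysis, since ten of 95 AECD patients came off the device. Nothing defines the phrase that way, and elsewhere the section compares groups.
- **Weight.** The endpoints are secondary, the selection is called exploratory, and the limit set by sample size is admitted. Even so, no non-exploratory survival comparison stands beside it.

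A cap on parameters per event, a penalised fit, or dropping the interaction tests would be matters of preference, not corrections of error.

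**Conclusion.** The point holds for the survival endpoints. As written, the sole survival analysis can end with no AECD odds ratio, with one kept only because it was significant, or with one adjusted for the effect's own pathway. The entry and removal limits are unworkable and need correcting, but they are the lesser fault.

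The size is illustrative: about 38% power, so roughly 60% of analyses without an arm estimate. It rests on survival rates by speed of shock standing in for the arms, and on 40 arrests per arm. Both are generous. With control times of 180 ± 180 s, many controls would be shocked within 3 minutes, which narrows the contrast. One event had occurred among 192 recruits when the article was written. The simulations also depend on the assumed number of null covariates, the distribution of times and the slopes. That selection does not guarantee an arm estimate, and that time to defibrillation is not excluded, follows from the wording and needs none of these assumptions.

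**What to change.** State that the effect on each survival endpoint is estimated from a logistic model that always includes the assigned arm. Limit any adjustment to a few pre-specified pre-arrest covariates. Report the arm's odds ratio and 95% CI whatever its p-value. Exclude time to defibrillation and other post-randomisation variables from that model.

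If a search for predictors is kept, label it as separate and exploratory, word both limits as 'p below', and set the removal limit no lower than the entry limit.

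The cost is a change of wording and fewer exploratory results. No data collection changes. Forcing the arm in adds no power; it ensures that an estimate with its uncertainty is reported.

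### The five-level CPC outcome is to be analysed in a 2 × 3 table with no stated merge, and the plan does not say whether the chi-square or the ordinal mean-score test decides

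*Protocol article*

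**What the plan says.** In the Protocol article, Methods makes CPC a secondary outcome: "The secondary outcomes are survival to discharge and cerebral outcomes as measured by cerebral performance category scale (Table 2"). Table 2 lists five ordered levels, from CPC 1 ("Good cerebral performance – conscious, alert, able to work, might have mild neurologic or psychological deficit") to CPC 5 ("Brain death – apnea, areflexia, EEG silence, etc").

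The Statistical analysis section refers back to Table 2 and says the outcome is measured on the "categorization (CPC) scale and analyzed initially using χ^2 ^tests". The next sentence begins "If cell counts warrant, the 2 × 3 contingency table will be analyzed using exact methods" and continues that "the mean score statistics (Q) will be used to compare cerebral performance status between the groups". The article describes no grouping of the five levels into three.

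The Sample size section gives the number per arm ("A total sample size of 40 patients per group will be recruited"). Its power statements concern time to defibrillation only.

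**The concern.** Three things do not fit together.

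- **Table and scale.** Two arms and five categories give ten cells. A 2 × 3 table has six. Some categories must be merged or dropped, and the article does not say which.
- **First test and type of scale.** Pearson's chi-square ignores the order of the categories. A device that moves patients towards better CPC levels produces an ordered shift, which chi-square spreads over several degrees of freedom. Q concentrates it on one.
- **Deciding test.** The opening condition on cell counts may govern only the exact methods, or Q as well. Nothing says which result decides if chi-square and Q disagree.

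At stake is a named secondary endpoint. If merge and test stay open until the data are seen, there are several chances at a significant result. If chi-square decides, power is lost.

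**Working it through.** **The plan's own figure.** The only stated power is for time to defibrillation. With a difference of 180 − 30 = 150 s and SD = √((30² + 180²)/2) = 129.03 s:

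- 12 per group: SE = 129.03 × √(2/12) = 52.68; 150/52.68 − 1.96 = 0.89; power 81.3%.
- 40 per group: SE = 129.03 × √(2/40) = 28.85; 150/28.85 − 1.96 = 3.24; power 99.9%.

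Both stated figures (81% and over 99%) reproduce by normal approximation. They say nothing about CPC.

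**CPC tests compared.** Pearson chi-square was computed on the non-empty columns. Q uses integer scores: Q = (f₁ − μ)² / [v·n₂ / (n₁(n − 1))] on 1 df, where f₁ is the mean score in arm 1, and μ and v are the pooled mean and variance of the scores. Both use two-sided 0.05 and asymptotic p-values.

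**Assumed inputs.** The article gives no CPC distribution or effect. Three control distributions over CPC 1–5 were assumed:

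- A: 15/6/5/4/70%
- B: 20% each
- C: 50/20/15/10/5%

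The device arm multiplies the cumulative odds by a common odds ratio (OR). For A with OR 3, P(CPC 1) = (3 × 0.15/0.85) / (1 + 3 × 0.15/0.85) = 34.6%. Each scenario has 40 arrests per arm and 40,000 trials. The 2 × 3 ranges cover the merges 1-2/3-4/5, 1/2/3-5 and 1/2-4/5.

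| Control, OR | 2 × 5 chi-square | 2 × 5 Q | 2 × 3 chi-square | 2 × 3 Q |
|---|---|---|---|---|
| A, 2 | 18.5% | 32.6% | 21.3–25.8% | 27.5–32.7% |
| A, 3 | 48.0% | 69.1% | 51.6–60.1% | 61.6–69.0% |
| B, 2 | 23.5% | 40.3% | 26.4–29.1% | 34.1–36.1% |
| B, 3 | 55.1% | 76.9% | 59.1–64.1% | 69.7–73.5% |
| C, 2 | 18.3% | 32.5% | 18.0–27.0% | 24.5–34.4% |
| C, 3 | 41.9% | 62.0% | 37.0–56.0% | 46.8–65.5% |

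The chi-square deficit on 2 × 5 runs from 32.6 − 18.5 = 14.1 to 76.9 − 55.1 = 21.8 points. Within one merge on 2 × 3 it is about 6 to 11 points.

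**A second set of assumptions.** Survivors' CPC is taken as 70/15/10/5% over levels 1–4, with deaths in category 5 (6,000 trials each). Survival of 22.2% against 39.3% is borrowed from the Discussion, which cites these figures for delayed and non-delayed defibrillation, not for trial arms. The 55% is purely assumed.

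| Table | 22.2% vs 39.3%: chi-square / Q | 22.2% vs 55%: chi-square / Q |
|---|---|---|
| 2 × 5 | 20% / 35% | 69% / 84% |
| 1-2/3-4/5 | 29% / 36% | 80% / 86% |
| 1/2-4/5 | 29% / 35% | 80% / 83% |
| 1/2/3-5 | 23% / 30% | 68% / 75% |

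The 2 × 5 gap is 15 points in both columns. The 2 × 3 gaps are 3 to 7 points from these rounded figures. Taking both sets together, the 2 × 3 deficit is about 3 to 11 points.

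**Cost of the open merge with Q alone.** In the first set, three columns instead of five cost Q between nothing and about 15 points. The largest loss is in C at OR 3 with 1-2/3-4/5: 62.0 − 46.8 = 15.2. The other two merges lose nothing there (65.5% and 63.6%).

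**Cost of leaving merge and test open.** Four merges (the three above and 1-2/3/4-5) with two tests give eight combinations. Under the second set of assumptions with no true effect, at least one reached p < 0.05 in 8.8% of trials. Q on any one fixed table in the first set stayed at about 5%. At 22.2% against 39.3% survival, the eight combinations did not all agree on significance in 28% of trials.

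**The case against.** The plan is better than a quick reading suggests, and several stronger inferences do not hold.

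- **That the plan ignores order.** A reader who stops at the first half of the key sentence might infer this. The second half names Q, an ordinal test. The power loss arises only if chi-square decides, and the text does not say that it does.
- **That the chi-square is invalid because cells are sparse.** Sparse cells are likely: under distribution A, 40 control arrests give expected counts of 6.0, 2.4, 2.0, 1.6 and 28.0. But the plan foresees exact methods according to cell counts. In simulation the 2 × 5 chi-square was conservative (1.8% null rejection under the second set of assumptions), so the harm is lost power and not false positives.
- **That the loss is about 15 points.** That figure belongs to a 2 × 5 chi-square, while the plan names a 2 × 3 table, where the gap is smaller. For two of the three merges in the second set, Q on three levels performs as well as Q on five.
- **That CPC will be compared among survivors only.** No passage restricts it so, and survival to discharge is analysed separately. The article is merely silent on where deaths other than brain death are placed.
- **That the merge will be chosen after seeing the data.** This is inferred from silence. An article condenses its protocol, and groupings are often fixed elsewhere.

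All of this stands and limits the point. It does not remove the contradiction: the article fixes a three-column table for a scale it defines with five levels, and gives two tests without an order of authority.

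**Conclusion.** The point holds in limited form. The table dimension contradicts the scale, and the deciding test for a named secondary endpoint is not fixed. No stated power figure is wrong, because none is given for CPC.

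If chi-square decided, the loss against Q would be about 14 to 22 points of power on a 2 × 5 table and about 3 to 11 on a 2 × 3 table. Leaving merge and test open raises the chance of at least one nominally significant result under no effect to about 9% in the scenario examined. These sizes rest on assumed CPC distributions and effects, on asymptotic tests, and on 40 arrests per arm. Preliminary results report one event among 192 patients, so 40 arrests per arm may be optimistic. The direction of the power comparison was the same in every scenario tried. This is worth correcting, but it does not touch the primary endpoint.

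**What to change.** Replace the two CPC sentences in Statistical analysis with a plan that:

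- keeps all five levels of Table 2, or defines one three-level merge in advance, and makes the stated table dimension match;
- names the exact mean-score (Q) test, with its scores, as the single deciding CPC analysis in place of the initial chi-square and without a condition on cell counts;
- scores every death before discharge in the worst category, so that all qualifying arrests are compared by assigned arm.

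The change is a few sentences and needs no new data. With one event in the AECD arm and none in the control arm at the time of the article, it could be made before outcomes could influence it. The downside is that equally spaced scores and the grouping of deaths with CPC 5 must be accepted. The category counts by arm, with deaths identifiable, should therefore be shown beside the test.
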